1In middle-aged adults, what are the acute (immediate) effects of uninterrupted sitting and frequent, short activity breaks during 3 h of sitting on cerebral blood flow in the prefrontal cortex?Our *secondary* research questions are:2In middle-aged adults, what are the acute (immediate) effects of uninterrupted sitting and frequent short activity breaks during 3 h of sitting on:(a)Cognitive performance?(b)Psychological factors (stress, mood, alertness, and sleepiness)?(c)Post-prandial blood glucose?3Does vascular health (arterial stiffness) attenuate the effects of activity breaks on cerebral blood flow?Based on previous research, we hypothesize that:(a)Changes in neural activity-related prefrontal cortex cerebral blood flow (hereafter termed cerebral blood flow) from pre-test to post-test will be greater following the conditions with frequent, short activity breaks compared with the uninterrupted sitting condition;(b)Cerebral blood flow will be greater post-intervention compared to pre-intervention for the frequent, short activity breaks conditions, but not for the uninterrupted sitting condition;(c)Improvements in cognitive performance will be larger in magnitude in the frequent, short activity breaks conditions compared with the uninterrupted sitting condition;(d)The frequent, short activity break conditions will lead to improvements in psychological factors, compared with the uninterrupted sitting condition;(e)Glucose levels will not differ between the conditions;(f)Arterial stiffness will temporarily decrease immediately after the frequent, short activity break conditions (compared to pre-test levels), but will not change after the uninterrupted sitting condition; and(g)Arterial stiffness will moderate the effect of frequent, short activity breaks on cerebral blood flow, such that participants with lower arterial stiffness at baseline will have greater cerebral blood flow after the frequent, short activity break conditions compared with participants with higher arterial stiffness.

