## Materials and Methods

### Design

A crossover randomized 3-condition experimental trial will be carried out with a target sample size of 13 participants. All study procedures will occur at the Swedish School of Sport and Health Sciences (GIH) in Stockholm, Sweden. Participants will be recruited from the general Swedish population using social media, GIH’s homepage, and newspaper advertisements. As well, through the Swedish Armed Forces’ personnel magazine and word of mouth. Participants will initially attend a familiarization session for the collection of demographic data, fitness testing, and acquaintance with experimental procedures. Each participant will undergo 3-h experimental conditions in random order, with a minimum washout period of 4 days between each of the three visits (Bell et al., 2018). Physical activity, sleep, and glucose levels will be measured for the 24 h before each condition. A computer-generated randomization schedule will be created before study commencement, and participants will be randomized to a condition order at the end of the familiarization session. This trial obtained ethical approval by the Swedish Ethical Review Authority, Stockholm, Sweden (Dnr 2019-00998). Trial registration for experimental studies of this nature is not required but is increasingly being recognized as good practice (English et al., 2020). Therefore, we registered this trial at www.clinicaltrials.gov (NCT04137211) on October 23, 2019, after recruitment began on May 13, 2019.

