### Outcome Measures

Outcome measures will be collected immediately before and immediately after each experimental condition.

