#### Cerebral Blood Flow

The primary outcome measure will be the changes in oxygenated hemoglobin (oxy-Hb) using a non-invasive multi-channel continuous-wave fNIRS instrument (portable NIRSport, 8–8 system, with short-separation channels, NIRx Medizintechnik GmbH, Berlin, Germany). The optodes will be positioned over the prefrontal cortex, with data sampled at 7.81 Hz at wavelengths 750 nm and 820 nm. The fNIRS cap has 16 channels created by eight LED light sources and 8 detectors placed according to the standard 10–20 system, with a source-detector separation distance of 3 cm. Additional short-separation optodes with a distance of 0.8 cm (NIRx Medizintechnik GmbH, Berlin, Germany) to account for superficial blood flow (Yücel et al., 2015) will also be used. We chose to measure cerebral blood flow in the prefrontal cortex region as working memory tasks (such as the n-back) predominately activate this region (Smith and Jonides, 1997; Owen et al., 2005). System calibration will be performed before each assessment using NIRStar 15.2 software and using the predefined montage, and the fNIRS signals will be visually quality checked during data collection for motion artifacts. Cerebral blood flow measures will be taken simultaneously while the participant performs three cognitive tasks of increasing workload (numerical 1-, 2-, and 3-back tests). Our primary outcome variables will be changes in oxy-Hb between the 1-back and 2-back and between the 1-back and 3-back tests (expressed in ΔμM). We will also record deoxygenated (deoxy-Hb) concentrations. Further details about system calibration and data processing are included in Supplementary Material.

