### Data Analysis

To answer our primary research question, linear mixed-effects models with subject as the random effect will be used to assess within condition differences in the changes in cerebral blood flow (oxy-Hb) between pre- and post-tests correcting for multiple comparisons from estimation over many channels, using Benjamini–Hochberg. Time and condition interactions will be used to estimate differences between conditions. Baseline arterial stiffness will be assessed as a moderator in the models. Linear mixed models will also be used to assess secondary outcomes, to investigate within-person changes from pre- to post-test, and between conditions. Stata version 15 (StataCorp, College Station, TX, USA) and NIRSToolboxAnalyzer (Santosa et al., 2018) will be used for statistical analyses.

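### Comparing conditions by the time-by-condition interaction is unbiased, but less precise than adjusting each post-test for that visit's pre-test, which the trial already collects

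*Protocol article*

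**What the plan says.** The Design section describes the trial as follows: "A crossover randomized 3-condition experimental trial will be carried out with a target sample size of 13 participants". Order is random, with at least 4 days between visits. Under Outcome Measures, "Outcome measures will be collected immediately before and immediately after each experimental condition", so each of the three visits has its own pre-test.

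For the primary question, the Data Analysis section says that "linear mixed-effects models with subject as the random effect will be used to assess within condition differences in the changes in cerebral blood flow". It then says how conditions are compared: "Time and condition interactions will be used to estimate differences between conditions". Linear mixed models are also planned for the secondary outcomes. The only baseline term named is a different variable: "Baseline arterial stiffness will be assessed as a moderator in the models".

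Hypothesis (a) in the Introduction is that changes "from pre-test to post-test will be greater following the conditions with frequent, short activity breaks compared with the uninterrupted sitting condition". Hypothesis (b) concerns the change within each condition. The primary variables are themselves differences, namely "changes in oxy-Hb between the 1-back and 2-back and between the 1-back and 3-back tests".

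**The concern.** In a crossover, stable differences between participants cancel when conditions are compared within a participant. The pre-test is therefore not needed for that purpose; its use is to remove noise specific to the visit. A change score does this with the slope fixed at 1, whatever the true relation between pre-test and post-test. Because order is random and the pre-test precedes the condition, the expected pre-test mean is the same in all three conditions. A covariate adjustment, or a constraint to equal pre-test means, uses that fact; an unconstrained interaction does not.

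Precision is at stake, with only 13 participants. The primary variable is a difference between task loads, which may make r low, and low r is where the loss is largest. The primary analysis is also corrected over many channels, which reduces power further.

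**Working it through.** **The plan's own figure.** The Sample Size section gives effect sizes of 0.9 to 2.4 and 6 to 13 participants, at two-sided α = 0.05 and a value of 0.8 labelled β (read here as power). A paired t-test gives n = 12 at 0.9 (power 81.0%; 84.5% at n = 13) and n = 4 at 2.4. That is close to the stated 13 and 6, though not identical. Nothing in that section refers to pre-test adjustment or supplies r.

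**Inputs.** From the article: 13 participants, three conditions, a pre-test and post-test at each visit, and the interaction as the between-condition estimator. Assumed: equal variances at pre-test and post-test, and r = 0, 0.2, 0.5 or 0.7. Let s² be the variance of one measurement after removing subject.

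**Variance of the contrast between two conditions, per participant.**
- Change scores (interaction): 2 × 2s²(1 − r) = 4s²(1 − r).
- Post-test adjusted for that visit's pre-test: 2s²(1 − r²).
- Ratio, adjusted to change: (1 − r²) / [2(1 − r)] = (1 + r)/2.

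This is below 1 for every r below 1. At n = 13 the slope must be estimated, so the gain is somewhat smaller. Simulation with subject, condition and period terms gives:

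| Assumed r | (1 + r)/2 | Simulated ratio, n = 13 | Narrowing of interval (1 − √ratio) | Power, from about 48% |
|---|---|---|---|---|
| 0 | 0.50 | about 0.52 | 28% | about 76% |
| 0.2 | 0.60 | about 0.64 | 20% | about 67% |
| 0.5 | 0.75 | about 0.79 | 11% | about 57% |
| 0.7 | 0.85 | about 0.89 | 6% | about 52% |

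Independent simulations agreed on the ratios to within about 0.03. Type I error of the adjusted analysis stayed near 5%. Power is for one contrast at two-sided 5%, before any correction over channels.

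**Standard error when subject is the only random effect.** Such a model treats all six values of a participant as equally correlated, which implies r = 0. With 13 participants there are 78 values. After 13 subject terms and 5 fixed terms, 60 residual degrees of freedom remain: 24 between visits, with variance s²(1 + r), and 36 within visits, with variance s²(1 − r).
- Pooled residual: [24(1 + r) + 36(1 − r)]/60 = 1 − r/5, in units of s².
- The interaction needs 1 − r.
- r = 0.5: 0.90/0.50 = 1.80, so the standard error is √1.80 = 1.34 times too large and type I error is about 0.9%.
- r = 0.7: 0.86/0.30 = 2.87, so the standard error is 1.69 times too large and type I error is about 0.1%.

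Simulation agrees: about 1% at r = 0.5, and 0.1% to 0.2% at r = 0.7. For effects that give about 48% power with correctly analysed change scores, the subject-only model has about 26% at r = 0.5 and 10% at r = 0.7.

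**The case against.** **The interaction answers the stated question, and no passage is contradicted.** Hypothesis (a) is worded as a difference in change, and the interaction estimates exactly that without bias. A reader might infer that the planned analysis is invalid; the article does not support that. The point is one of efficiency. Hypothesis (a) remains answerable after adjustment, because with equal expected pre-tests both estimators target the same effect.

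**The article is condensed.** A pre/post model with equal pre-test means is also a time-by-condition model, so the published sentence does not exclude it, and a fuller plan might specify it. This is fair as far as it goes. However, the article names the estimator and the random effect, and the constrained version is not what it states.

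**Subtraction is not always harmful.** A reader might infer that subtracting the pre-test adds variance whenever r is below 1. That holds only against baseline adjustment. Against the post-test alone the comparison is 4s²(1 − r) with 2s², a ratio of 2(1 − r), so subtraction adds variance only when r is below 0.5. At r = 0.7 it cuts variance to 60% of the post-test-only value.

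**The size is unknown.** The article gives neither r nor the reliability of the fNIRS contrast. Large-sample ratios would suggest power of about 62% to 71% for r of 0.5 to 0.2, but at n = 13 it is about 57% to 67%. At r = 0.7 the gain is only a few points, and near r = 1 it is negligible. If the true standardised effect on the change-score contrast is 0.9, a single correctly analysed contrast has 84.5% power at n = 13 without adjustment.

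**Equal pre-test means could fail for self-reports.** Order is assigned at the end of familiarization, and the article does not say whether participants know the day's condition before the pre-test. If they do, expectation could shift pre-test mood, alertness or sleepiness. This stands, and it limits where the constraint should be used.

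**Conclusion.** The point holds as a loss of precision, not as bias. For between-condition contrasts, adjusting for the visit's pre-test reduces the variance to between about 0.52 (r = 0) and 0.89 (r = 0.7) of the change-score variance at n = 13. The gain is material at low r and small at high r. High r does not rescue the plan as literally worded, because a model with subject as its only random effect then overstates the standard error of the interaction.

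These figures rest on an assumed r, equal pre-test and post-test variances, random order without carryover, and reading the Data Analysis section as an unconstrained interaction with no visit-level random effect. With 13 participants and a nearly free remedy, the change should be made.

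**What to change.** For hypothesis (a), and for every secondary outcome with a pre-test at each visit, specify one of these for the between-condition contrasts:

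1. Post-test as outcome; condition, visit number, that visit's pre-test and the participant's mean pre-test as fixed effects; participant as random effect.
2. The pre/post model with pre-test means constrained equal across conditions, and a visit-within-subject random effect added to the subject effect.

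For self-reported outcomes prefer option 1, since the constraint in option 2 could fail if participants know the day's condition before the pre-test.

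Keep the pre-post contrast for the within-condition question (hypothesis (b)), which a post-test-only outcome does not answer directly. Keep the unconstrained interaction as a sensitivity analysis, with a visit-within-subject effect so that its standard error is right.

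The cost is a change of wording and one or two degrees of freedom. No new data are needed. If r turns out to be near 1, little is gained.

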## Discussion

Short, frequent bouts of physical activity may be a promising strategy to increase cerebral blood flow to counteract the negative effects of extended periods of sitting. This crossover randomized trial will determine the effects of frequent, short bouts of physical activity on cerebral blood flow and cognitive performance, as well as psychological factors, and blood glucose levels. This topic is important considering that people are spending increasingly longer periods sedentary each day, particularly in their workplaces (Parry and Straker, 2013), which could potentially lead to long-term unfavorable effects on cognitive function (Voss et al., 2014; Wheeler et al., 2017).

This trial has many strengths. The randomized crossover design reduces contamination and the trial is powered to detect meaningful differences in cerebral blood flow. Importantly, our fNIRS protocol includes short-separation channels to remove superficial blood flow from measures of cerebral blood flow. The use of device-based measures of physical activity, sedentary behavior, and sleep and the use of a VO_2max_ fitness test to personalize the physical activity walking bout are further strengths. The 3-h duration of uninterrupted sitting was chosen as it has high ecological validity; in a cross-sectional study of 334 adults of mean age 42 years, participants rarely sat for longer than 3 h at a time (Bojsen-Moller et al., 2019).

The two exercise paradigms we selected are readily applicable to the workplace setting. If we find immediate effects of physical activity on cerebral blood flow, the next steps would be to develop and test workplace interventions to examine the long-term effects of these paradigms and determine the clinical significance of cerebral blood flow changes on other factors such as productivity, concentration, and cognitive decline.

Finally, this protocol article will contribute to increasing scientific rigor in understanding how immediate, frequent, short activity bouts can affect cerebral blood flow since only one of the previous trials with similar aims has been registered or has published their protocols (Wennberg et al., 2016). Future studies should consider registering and publishing protocols to reduce negative findings not being published and to avoid potential bias of future reviews.
